## Abstract

**Background:**

Frailty and prefrailty are highly prevalent conditions among older adults and are associated with increased functional decline, fall risk, hospitalization, and mortality. Multicomponent supervised exercise programs have demonstrated efficacy in improving physical performance and mitigating frailty, particularly when adapted to older adults’ functional capacity. However, evidence regarding Vivifrail-based interventions for frail and prefrail older adults in Brazil remains limited.

**Objective:**

This study aims to evaluate the effects of a 12-week supervised multicomponent exercise program on functional capacity and fall risk among frail and prefrail older adults. Additionally, the study aims to characterize participants according to frailty status, clinical-functional vulnerability, cognitive status, depressive symptoms, physical activity level, muscle mass, fear of falling, and sociodemographic and clinical characteristics at baseline.

**Methods:**

This study protocol describes a prospective, parallel-group, single-blind randomized controlled trial. Older adults aged 60 years and older who regularly attend activities at the CONVIVER Community Center in Rio Verde, Goiás, Brazil, will be screened and randomized in a 1:1 ratio into either an intervention group or a control group. The intervention group will participate in a supervised multicomponent exercise program based on the Vivifrail model for 12 weeks, whereas the control group will participate in health education workshops focused on healthy aging. The primary outcomes will be functional capacity, assessed using the 6-Minute Walk Test, and fall risk and mobility performance, assessed using the Timed Up and Go Test. Baseline assessments will additionally include frailty status (Edmonton Frailty Scale), Clinical-Functional Vulnerability Index-20, cognitive status (Mini-Mental State Examination), depressive symptoms (Geriatric Depression Scale-15), physical activity level (International Physical Activity Questionnaire), calf circumference, fear of falling (Falls Efficacy Scale-International), and sociodemographic and clinical characteristics.

**Results:**

Recruitment and baseline assessments are planned to occur between July and December 2026 at the CONVIVER Community Center. A total of 70 participants are expected to be enrolled and randomized into the intervention group (n=35) or the control group (n=35). At the time of manuscript submission, participant recruitment had not yet started, and no outcome data had been collected or analyzed. Final results are expected to be published in late 2027.

**Conclusions:**

This randomized controlled trial protocol describes a supervised multicomponent exercise intervention tailored to frail and prefrail older adults in a Brazilian community setting. If effective, the intervention may represent a feasible, low-cost, and scalable strategy to improve functional capacity and reduce fall risk in vulnerable older populations while supporting evidence-based healthy aging initiatives.

## Introduction

The global demographic transition toward an aging population represents one of the most significant public health challenges of the 21st century. By 2050, the number of individuals aged 60 years and older is expected to exceed 2.1 billion, with the greatest growth occurring in low- and middle-income countries [1]. This demographic shift is accompanied by an increased prevalence of age-related conditions, including frailty, sarcopenia, functional decline, and falls, which negatively affect independence, quality of life, and health system sustainability [2].

Functional decline and fall risk are particularly relevant public health concerns. Falls are the second leading cause of accidental injury-related deaths worldwide and are associated with substantial physical and psychosocial consequences [3]. Factors such as muscle weakness, postural instability, and sensory deficits contribute significantly to fall risk, highlighting the need for effective preventive strategies [4].

Frailty and prefrailty are key indicators of vulnerability in older adults. Frailty is a multidimensional geriatric syndrome characterized by reduced physiological reserves across multiple systems, increasing susceptibility to stressors such as illness and environmental challenges [5]. Prefrailty represents an intermediate and potentially reversible stage preceding frailty. Among older adults, frailty affects approximately 10% to 15%, while prefrailty may occur in up to 50% [6]. Both conditions are associated with adverse outcomes, including disability, hospitalization, institutionalization, and mortality [7], and are linked to systemic inflammation, immune dysregulation, and sarcopenia [8,9].

Frailty is also strongly associated with an increased risk of falls [3]. In Brazil, falls constitute a major public health issue and are among the leading causes of hospitalization in individuals aged 65 years and older [10]. Given their multifactorial nature, frailty and fall risk require multidimensional preventive approaches. Physical exercise is one of the most effective nonpharmacological strategies for reducing frailty, improving physical function, and promoting healthy aging [11,12]. Regular physical activity reduces chronic disease risk and mortality, whereas sedentary behavior increases the likelihood of dependence, falls, and fractures [13].

Multicomponent exercise programs that combine aerobic, strength, balance, and flexibility training are particularly effective in older populations [13]. These programs improve muscle strength, mobility, postural control, and cardiorespiratory capacity, thereby reducing functional decline and fall risk [14,15]. However, despite growing evidence, studies vary considerably in design and target populations, limiting their generalizability [16,17]. Group-based and supervised interventions appear to enhance adherence and functional outcomes, especially among frail individuals [18-20].

The Vivifrail program, developed within the European Erasmus+ initiative, provides an individualized, function-based exercise prescription tailored to older adults’ performance levels [21]. Evidence suggests that Vivifrail-based interventions can reverse frailty, improve cognition and mood, and prevent functional decline related to hospitalization [22-24]. Nevertheless, its application in Latin America, particularly in Brazilian community settings, remains limited, and randomized controlled trials (RCTs) in this context are scarce [20].

To address these gaps, this study aims to evaluate the effects of a 12-week supervised multicomponent exercise program on functional capacity and fall risk among frail and prefrail older adults. In addition, the study described in this protocol aims to characterize participants according to frailty status, clinical-functional vulnerability, cognitive status, depressive symptoms, physical activity level, muscle mass, fear of falling, and sociodemographic and clinical characteristics at baseline. Its findings aim to support the development of evidence-based, culturally tailored interventions to promote healthy aging in these populations.

## Methods

### Study Design

This study is a prospective, parallel-group, single-blind RCT. The study will be conducted in accordance with the SPIRIT (Standard Protocol Items: Recommendations for Interventional Trials) guidelines. Ethical approval was obtained from the Ethics and Research Committee of the University of Rio Verde (6,658,796; February 20, 2024), and all procedures will follow the ethical principles of the Declaration of Helsinki and its subsequent amendments. Written informed consent will be obtained from all participants prior to enrollment. The clinical trial was prospectively registered with the Brazilian Registry of Clinical Trials under number RBR-9zvtc5b on June 26, 2024.

This protocol was submitted before the initiation of participant recruitment, intervention implementation, data collection, and outcome analysis. At the time of manuscript submission, no study outcomes had been collected or analyzed. The protocol publication aims to ensure methodological transparency, reproducibility, and external peer review before the completion of the clinical trial.

The trial will be conducted at the CONVIVER Community Center for Older Adults, a publicly funded facility located in Rio Verde, Goiás, Brazil, which provides free physical, social, and health-promotion activities for older adults. Participants will be randomly allocated to one of the two groups: (1) a supervised multicomponent exercise group based on the Vivifrail protocol or (2) a control group receiving twice-weekly health education workshops focused on healthy aging topics. The study flow diagram is presented in Figure 1.

**Figure 1. F1:**
[figure not shown]
Flow diagram of the study protocol. EFS: Edmonton Frailty Scale; MMSE: Mini-Mental State Examination.

### Screening and Recruitment

Screening, recruitment, and baseline assessments are planned to occur between July and December 2026 at the CONVIVER Center facilities. Recruitment will occur exclusively at the center during routine activities regularly attended by older adults already enrolled in the institution. Potential participants will be approached by members of the research team and invited to receive detailed information regarding the objectives, procedures, risks, and benefits of the study.

### Participants

Participants will consist of older adults who regularly attend activities offered by the CONVIVER Community Center for Older Adults in Rio Verde, Goiás, Brazil. The CONVIVER Center is a publicly funded community facility coordinated by the municipal government that provides social, educational, recreational, and health-promotion activities for independently living older adults from the local community.

Individuals who express interest in participating will undergo eligibility screening and baseline assessments after signing the written informed consent form. During the screening phase of the study, frailty status will be assessed to determine the participants’ eligibility.

Inclusion criteria will include (1) age of 60 years or older; (2) living independently in the community; (3) regular participation in activities offered by the CONVIVER Community Center; (4) classification as prefrail or frail according to the Edmonton Frailty Scale (EFS); (5) preserved cognitive function sufficient to understand the study procedures, as assessed using the Mini-Mental State Examination (MMSE); and (6) clinical ability to participate safely in supervised physical exercise activities.

Exclusion criteria will consist of (1) acute or unstable cardiovascular conditions; (2) severe neurological, orthopedic, or musculoskeletal impairments limiting safe exercise performance; (3) severe visual, auditory, or communication impairments compromising assessment procedures; (4) recent hospitalization or clinical instability within the previous 3 months; (5) inability to complete the assessment procedures; and (6) refusal to participate or withdrawal of informed consent at any stage of the study.

Frailty status will be determined using the EFS. Participants scoring between 5 and 6 points will be classified as prefrail, whereas those scoring 7 points or higher will be classified as frail. Individuals scoring between 0 and 4 points, indicating the absence of frailty, will not be eligible for participation in the study [25,26]. Participants attending fewer than 75% of intervention sessions will be considered nonadherent for per-protocol analyses but will remain eligible for intention-to-treat analyses whenever possible.

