### Randomization

After the completion of eligibility screening and baseline assessments, participants will be randomly allocated in a 1:1 ratio to either the supervised multicomponent exercise group or the health education control group. Before randomization, participants will be stratified according to frailty status, classified as prefrail or frail based on the EFS, to promote a balanced distribution of frailty levels between groups.

The randomization process will be performed using the online platform Research Randomizer by an independent researcher who will not participate in participant recruitment, assessments, intervention delivery, or data analysis [27]. Allocation concealment will be ensured through sequentially numbered, opaque, sealed envelopes prepared in advance by the independent researcher.

After baseline assessments, the next sequential envelope will be opened by a research assistant who is not involved in outcome assessment procedures. Participants will then be informed of their assigned group and referred to the corresponding intervention procedures.

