#### Intervention Group

Participants in the intervention group will engage in a supervised physical exercise program based on the Vivifrail protocol [21]. The program will span 12 weeks, with sessions held twice weekly, totaling 24 sessions, each lasting approximately 45 minutes, and will include exercises targeting strength, balance, mobility, gait, flexibility, and functional endurance. The sessions will be conducted in small groups under the direct supervision of trained physiotherapists, as described in Figure 2.

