Physiological responses and clinical symptoms, including excessive fatigue, dizziness, pain, dyspnea, and cardiovascular symptoms, will also be monitored throughout the sessions to ensure participant safety. Progression of the exercise program will occur gradually throughout the intervention period according to individual adaptation and tolerance. Strength exercises will be progressed by increasing the number of repetitions when participants demonstrate adequate performance and safety. Balance and mobility exercises will be progressed through the reduction of external support.

To ensure intervention fidelity and reproducibility, all physiotherapists involved in the intervention will receive standardized training regarding exercise prescription, progression criteria, monitoring procedures, and safety management before the beginning of the trial. Standardized exercise protocols and progression checklists will be used throughout the intervention period. Attendance will be recorded at each session, and adherence rates will be monitored continuously. Any adaptations, interruptions, AEs, or deviations from the intervention protocol will be systematically documented by the research team.

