#### Control Group

Older adults allocated to the control group will participate in a series of workshops focused on healthy aging–related topics. These workshops will be conducted on-site at the CONVIVER Community Center and will provide educational content and practical guidance aimed at promoting health, autonomy, self-care, and quality of life among older adults. Topics addressed during the workshops will include healthy lifestyle habits, fall prevention, chronic disease management, nutrition, medication use, mental health, sleep quality, and strategies to maintain independence during aging.

The workshops will occur twice weekly in parallel with the intervention group activities, with each session lasting approximately 45 minutes (Figure 3). This comparator was selected because the CONVIVER center routinely offers health education and social support activities as part of standard community care for older adults. Therefore, participants allocated to the control group will continue receiving usual community-based care and social interaction throughout the study period.

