### Statistical Analysis

For the statistical analysis, data normality will be assessed using the Shapiro-Wilk test and Q-Q plots. Descriptive statistics will be performed to characterize the sample. Categorical variables will be presented as absolute and relative frequencies, whereas continuous variables will be expressed as means and SDs or medians and IQRs, in addition to graphical representations. Changes in mean values over time will be represented by delta values (Δ).

The primary analytical model for the 2 primary outcomes (6MWT and TUGT) will be an analysis of covariance, comparing postintervention values between groups while adjusting for the corresponding baseline values. Preintervention and postintervention comparisons will be conducted using the 2-tailed paired Student *t* test for normally distributed variables or the Wilcoxon signed-rank test for nonnormally distributed variables. Between-group differences will be analyzed using the independent Student *t* test for normally distributed variables and the Mann-Whitney *U* test for nonparametric variables.

Effect sizes will be calculated using eta squared (η²) and Cohen *d* and interpreted as small (0.2), medium (0.5), or large (0.8). All losses to follow-up and their respective treatment durations will be recorded for intention-to-treat analysis. All participants will be reassessed after the 12-week intervention period whenever possible. Missing data will initially be explored to determine the pattern and mechanism of missingness. When appropriate, missing outcome data will be handled using multiple imputation methods based on chained equations. Sensitivity analyses will be conducted to compare the results obtained from complete-case analyses and imputed datasets in order to evaluate the robustness and consistency of the findings. In addition, per-protocol analyses will be performed as secondary sensitivity analyses to assess the influence of adherence to the intervention on study outcomes. A significance level of *P*<.05 will be adopted for all statistical tests. Statistical analyses will be performed using the SPSS, version 25.0 (IBM Corp) [51], and graphs will be generated using R software (R Foundation for Statistical Computing) [52].

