### Safety Assessment and Withdrawal

Participant safety will be monitored throughout the intervention period by the research team and supervising physiotherapists. Any AEs potentially associated with the exercise sessions or assessment procedures, including dizziness, pain, excessive fatigue, musculoskeletal discomfort, falls, cardiovascular symptoms, or any other clinical complaints, will be immediately documented and evaluated.

If a participant develops any AE or clinical instability during the intervention period, exercise participation will be temporarily interrupted, and the participant will be closely monitored by the research team. When necessary, the participant will be referred for medical evaluation before resuming study activities. In cases where symptoms persist, recur after reintroduction of the intervention, or compromise participant safety, the participant may be withdrawn from the study after clinical assessment by the investigators. All AEs and safety-related occurrences will be systematically recorded in standardized monitoring forms throughout the trial period.

Participants will be free to discontinue their participation at any moment and for any reason, including the option to request the removal of their data from the study. Individuals will be considered withdrawn if they formally request to leave the trial or are lost to follow-up. Participants allocated to the intervention group will be classified as withdrawn if they discontinue participation in the supervised exercise program. Participants allocated to the control group will be classified as withdrawn if they discontinue participation in the educational workshops before the completion of the study.

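### The 75% attendance rule for the per-protocol set reads as covering the exercise arm only, so this secondary comparison could be distorted by one-arm selection after randomisation

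*Protocol article*

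**What the plan says.** Four parts of the protocol article bear on this.

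- **Threshold.** Methods, Participants: "Participants attending fewer than 75% of intervention sessions will be considered nonadherent for per-protocol analyses", "but will remain eligible for intention-to-treat analyses whenever possible".
- **Purpose.** Methods, Statistical Analysis: "per-protocol analyses will be performed as secondary sensitivity analyses to assess the influence of adherence to the intervention on study outcomes". The primary model there is an analysis of covariance on the post-intervention value, adjusted for the baseline value of the same outcome.
- **Sessions.** The exercise programme runs for 12 weeks "with sessions held twice weekly, totaling 24 sessions, each lasting approximately 45 minutes" (Intervention Group). For controls, "The workshops will occur twice weekly in parallel with the intervention group activities" (Control Group), also for about 45 minutes each.
- **Recording and interruption.** "Attendance will be recorded at each session, and adherence rates will be monitored continuously" appears under Intervention Group only. Safety Assessment and Withdrawal says that after an adverse event or clinical instability "exercise participation will be temporarily interrupted". The same section classes exercisers who stop the programme, and controls who stop the workshops, as withdrawn. It does not link either class to the per-protocol set.

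**The concern.** A per-protocol comparison is not protected by randomisation, because membership depends on what happens afterwards. The problem is sharper when the filter acts on one arm. Exercisers who attend little are removed, and their counterparts among the controls, who would also have attended little, stay in. If low attendance goes with worsening health, the remaining exercisers are a healthier group than the controls they are compared with. Baseline adjustment does not remove selection on changes in health after baseline.

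The stake is interpretation. This analysis is given the task of showing how adherence influences the outcomes. A per-protocol estimate above the intention-to-treat estimate would be read as a sign that attending more brings more benefit, and one-arm selection can produce that pattern when exercise has no effect.

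**Working it through.** **Step 1: what the threshold means in sessions.** 12 weeks x 2 = 24 sessions, and 0.75 x 24 = 18. A participant who misses 6 sessions still qualifies (18/24 = 75%). One who misses 7 does not (17/24 = 70.8%).

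**Step 2: which arm the rule covers.** Set side by side:

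- Towards exercise only: the arms are named intervention group and control group; control sessions are called workshops; attendance recording is described under Intervention Group; the stated purpose is adherence to the intervention.
- Towards both arms: the threshold sentence says participants and names no arm; under Randomization, both arms are told "Participants will then be informed of their assigned group and referred to the corresponding intervention procedures"; under Control Group, the control programme is itself called an intervention, one without exercise.

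Exercise only is the more natural reading, but the text does not settle it. On either reading no recording of workshop attendance is described.

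**Step 3: size of the shift on the exercise-only reading, with no true effect.** Inputs that the article does not give, and so are assumed:

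- q, the share of exercisers below 75%: 15%, 25%, 35%
- g, the correlation between attendance propensity and the part of the outcome not explained by baseline: 0.2 to 0.4
- r, the baseline-to-post correlation: 0.7

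With a normal attendance propensity cut at its q-quantile z, the mean shift in the retained exercisers, in SDs of the post-intervention outcome, is

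shift = g x phi(z)/(1 - q) x sqrt(1 - r^2), with sqrt(1 - 0.49) = 0.714.

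| q | phi(z)/(1 - q) | shift, g = 0.2 | shift, g = 0.4 |
|---|---|---|---|
| 15% | 0.233/0.85 = 0.274 | 0.039 | 0.078 |
| 25% | 0.318/0.75 = 0.424 | 0.061 | 0.121 |
| 35% | 0.370/0.65 = 0.570 | 0.081 | 0.163 |

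Against the design effect of 0.56 (Sample Size): 0.039/0.56 = 7% and 0.163/0.56 = 29%.

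**Step 4: simulation check and sensitivity.** 35 per arm, no true effect, baseline-adjusted analysis of covariance, r = 0.7, 3,000 runs. Entries are mean estimates in SD.

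| g in exercise / control arm | q | rule in exercise arm only | same rule in both arms |
|---|---|---|---|
| 0.3 / 0.3 | 10%, 20%, 30% | 0.04, 0.07, 0.10 | about 0 |
| 0.5 / 0.5 | 10%, 20%, 30% | 0.06, 0.13, 0.18 | about 0 |
| 0 / 0 | 10%, 20%, 30% | about 0 | about 0 |
| -0.3 / -0.3 | 10%, 20%, 30% | -0.04, -0.08, -0.10 | about 0 |
| 0.3 / 0 | 30% | 0.11 | 0.11 |

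At g = 0.5 and q = 30%, the two-sided 5% test rejects in 15% of runs with the exercise-only rule and in 4% with the rule in both arms. The last row matters for the remedy: where attendance is related to outcome in the exercise arm alone, a matching rule for controls removes nothing.

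**The case against.** The strongest reply has four parts.

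- **The rule names no arm, and a full per-protocol definition is commonly left to an analysis plan.** This stands in part. An incomplete definition alone would be no finding. But the article itself fixes the threshold, in words that most naturally filter one arm.
- **Controls are not untouched.** A reader might infer that every control stays in the per-protocol set. The documents do not support that: controls who stop the workshops are classed as withdrawn, and whether they are kept is not said.
- **The direction is not established.** A reader might infer that the per-protocol estimate must favour exercise. It does so only if attendance and outcome are positively related, and the article gives no figure. Nor does it follow that everyone interrupted for an adverse event is removed. Interruption is temporary, and six sessions, or three weeks, can be missed without falling below the threshold.
- **Little depends on it.** This stands. The analysis is a secondary sensitivity analysis, and non-adherent participants remain eligible for intention-to-treat. Secondary status limits the damage, but it does not make the estimate suitable for showing the influence of adherence.

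**Conclusion.** The point holds as a minor one. On its natural reading the rule selects exercisers alone on attendance after randomisation, and the handling of withdrawn participants is unstated for both arms. The resulting shift could be about 0.04-0.16 SD in favour of exercise when exercise does nothing. This rests on assumed non-adherence of 15-35%, an attendance-outcome correlation of 0.2-0.4 and a baseline correlation of 0.7. It vanishes at zero correlation and changes sign at a negative one.

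Two further inferences should be resisted. The primary intention-to-treat analysis of covariance is not put in doubt. And a symmetric rule would not make the per-protocol estimate unbiased: it helps when absence has the same drivers in both arms, and not when the reasons are specific to exercise.

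**What to change.** Recruitment has not started, so the change can be made before any data exist.

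1. In Participants, state that the per-protocol set requires at least 18 of the 24 scheduled sessions of the assigned programme, exercise or workshop.
2. Keep an attendance register for the workshops.
3. State how participants classed as withdrawn are handled in the per-protocol set, in the same way for both arms.
4. Analyse the set with the primary model, adding as a covariate the frailty stratum used in randomisation.
5. Label the result as a non-randomised comparison.
6. Report beside it a complier-average estimate: the intention-to-treat difference divided by the proportion of the exercise arm attending at least 18 exercise sessions. The denominator must count exercise sessions alone. Controls are offered the programme only after the post-intervention assessments, so their proportion is zero. If sessions of either programme were counted, the difference between arms could be near zero and the ratio would be unusable.
7. State the assumption behind that estimate: attending fewer than 18 sessions has no effect. If partial attendance helps, the estimate is too large.

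The cost is a workshop register, a few sentences and one added secondary analysis. The per-protocol set becomes smaller: if 15-35% fall below the threshold, about 30 to 23 of 35 remain in an arm (35 x 0.85 = 29.8; 35 x 0.65 = 22.8). The complier-average interval is wider than the intention-to-treat interval by a factor of about 1/0.85 = 1.18 to 1/0.65 = 1.54, before allowing for uncertainty in the attendance proportion.
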